### **4.8. Ensuring data quality**

#### 4.8.1. Monitoring

Monitoring is carried out at the trial centres to ensure the quality of the trial. The aim of monitoring is to verify the safeguarding and protection of the rights and safety of trial participants, the validity, verifiability and completeness of the trial data and the compliance of the trial conduct with the trial protocol, GCP and the applicable legal provisions.

All investigators agree that the monitor shall visit the study site at regular intervals and that the study sites shall provide the investigator with the necessary information. This is agreed in the

study site contracts. A corresponding passage is included in the declaration of consent (see Section 5.4), which grants the monitor the right to compare the documentation forms (CRF) with the original documents (medical records, ECG, laboratory printouts, etc.), taking into account the Data Protection Act. The auditors allow the monitor direct access to all necessary documents for the purposes of audit-related monitoring. The purpose of these visits is in particular:

- checking the informed consent forms,
- Patient safety checks (occurrence and documentation of complications)
- checking the CRFs for accuracy and completeness,
- the validation of CRFs against the original data (Source Data Verification, SDV)
- the evaluation of the progress of the examination,
- Checking compliance with the study protocol,
- GCP-compliant conduct of the study at the study site
- Discussion with the investigator about the conduct of the study and any deficiencies identified

A monitor report is prepared for each visit, which documents the progress of the clinical trial and provides information on any difficulties encountered (e.g. refusal of access).

The exact scope and type of monitoring are described in a separate monitoring manual..

#### 4.8.2. Audits/Inspections

The sponsor has the right to conduct audits at the study sites and other facilities involved in the trial as part of quality assurance. The aim of audits is to check the validity, verifiability and completeness of the data and the credibility of the clinical trial as well as to check the safeguarding of patient rights and the guarantee of patient safety. The sponsor may commission persons who are not otherwise involved in the clinical trial (auditors) for this purpose. These persons are permitted to inspect all trial-related documents (in particular: Study protocol, data collection forms, patient files, documentation of study medication, study-related correspondence).

The sponsor and all participating study sites undertake to support auditors, inspections by competent authorities and, in this context, to grant the authorised persons access to the original documents.

All persons carrying out audits undertake to treat personal data and other data confidentially.

#### **4.9. Documentation**

All study-relevant data is promptly recorded by the responsible investigator in the documentation forms (CRF) provided. The documentation can be delegated to other members of the study team. The survey forms are signed personally by the investigator. The information on patient satisfaction is only documented in the CRF, so that this part of the CRF serves as the source document. All other data recorded in the CRF is taken from the patient file.

##### **4.9.1. Data management**

In this study, the primary data collection is carried out using paper-based documentation forms. The data collected will be entered into a database at the IFOM. The data is entered using a data management programme that meets the FDA requirements according to 21 CFR part 11. The programme has an audit trail for tracking the entries and a role allocation for the users (data manager, data entry, monitors, etc.). The software is integrated into an IT infrastructure with an appropriate security concept and backup system. The electronic database is set up by the IFOM's data management team. The study-specific system, i.e. the documentation forms and the data collected with them, are validated. In addition, check processes are defined for the input (edit or validation checks in the front end or back end). After the validation process, the data is finally entered into a production version. This means that an electronic check sheet set that can only be used at IFOM is used for data entry. Details on the implementation of the data management system, the validation and checking processes are defined in the data management SOPs and in the data management plan.

The first step in processing the data in data management is to register and secure the incoming paper-based test forms. For this purpose, a copy of the test forms is stored in electronic form on an external server. The data is then entered by trained data entry staff. During data entry, the data is checked again by the data entry staff or the data management programme's checking system. In the event of queries, missing values or discrepancies, specific queries are sent to the centre. A separate query process is started for this purpose. The queries are registered and sent to the study sites. The responses confirmed by the investigator are entered into the database. In addition to the data providers, the monitors also use this query process for queries that cannot be clarified directly at the centre. Furthermore, there are corrections that can be made independently by the data entry person. The circumstances under which these can be carried out are specified in writing. The term "self-event corrections" refers to corrections that affect free text, for example, or that no longer require a query process in an

unambiguous situation. Example: standardised input of free text with regard to upper and lower case, if the examining physicians have only used capital letters, input of free text umlauts as ü=ue, ö=oe, ä=ae etc., in order to problems when converting the texts into other database formats. Standardised information if e.g. units are used, e.g. "mg/l" and not "mg / l" or similar. If a field is filled in but the corresponding yes/no query has not been specified, i.e. if it is clear that the answer can clearly only be "yes" or "no" (this procedure was suggested by an auditor in other studies). All so-called "self event corrections" are set out in writing in a list or a "Note To File" (see second case). As rule, this list is created during the test entry of study data. The list is signed off by the project and data manager. The data entry persons are trained in this regard. The data entry persons may only enter data within the scope of these defined "corrections". It is not possible to correct the content.

#### *4.9.1.1. CRF: Demographic data and preoperative data*

(Screening/inclusion, collection in consultation or outpatient clinic or consultation, missing data can be added during preoperative preparation (e.g. medication))

- Demographic data
  - Date of birth
  - Gender
  - Size
  - Weight
  - BMI
- Inclusion criteria:
  - Primary, bilateral inguinal hernias (if necessary, imaging confirmation by sonography/CT/MRI), if necessary, indication if one hernia is larger than the other (should "randomise out" in the end anyway)
  - Patient suitable for laparoscopic hernia surgery
  - Age >18
- Exclusion criteria:
  - Recurrent hernia
  - Incarcerated hernia
  - Acute systemic infection
  - Expected non-compliance with any study requirement
  - Severe comorbidity (ASA >=4)
  - Life expectancy <12 months
  - Chemotherapy within the last 4 weeks

- Radiotherapy within the last 2 months
  - Known allergy to pig or bovine antigens
  - Simultaneous participation in another study that interferes with this study
  - Previous participation in this study
- Pain according to VAS (0-10) separated by side
  - At rest
  - Under strain (coughing/pressing)
- Previous abdominal operations (e.g. appendectomy, cholecystectomy, etc.) with year of previous operation
- Concomitant diseases (e.g. CHD, diabetes mellitus, tumours, etc.)
- Concomitant medication incl. medication on demand
- ASA-classification

#### *4.9.1.2. Preoperative preparation (D-3 bis D-1)*

- Pain according to VAS (0-10) separated by side
  - At rest
  - Under strain (coughing/pressing)
- Information/consent

#### *4.9.1.3. CRF: Operation data*

- Randomisation
- Patient treated as randomised?
- Date
- Duration of surgery (incision-suture)
- ASA classification
- Antibiotic prophylaxis yes/no?
- Adhesiolysis necessary yes /no
- Type of hernia (per side)
  - Medial/ lateral/ combined (classification according to Schumpelick)
  - Size (1=<1.5 cm, 2=1.5-3 cm, 3=>3 cm, classification according to Schumpelick)
- Drainage yes/no
- Fixation of the mesh yes/no, which adhesive
- Complications
  - Intestinal injury

- Bleeding incl. severity (mild/ moderate/ severe)
  - Injury to the bladder
  - Conversion
- Further interventions:
  - Removal of Meckel's diverticulum
  - Simultaneous umbilical hernia operation
  - other

#### 4.9.1.4. CRF: hospital course/discharge (D2-D4)

- Number of inpatient treatment days
- Drainage removal when (if drainage inserted)
- Wound healing of the surgical accesses regular?
- Pain according to VAS (0-10) separated by side
  - At rest
  - Under strain (coughing/pressing)
- If sonography is performed (optional, not mandatory)
  - Seroma/haematoma laterally separated
  - mesh dislocation laterally separated
- Complications
  - Infection (local/systemic)
  - Seroma/Haematoma
  - Thromboembolism
  - Ileus
  - Revision operation separated laterally
  - mesh dislocation laterally separated
  - other
- Patient satisfaction
- Feeling of foreign body yes/no separated from the side
- Paraesthesia yes/no separated by side

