#### 4.6.3. Method for assigning patients to the treatment groups and blinding

All patients included in the study are assigned a unique patient identifier. This consists of the abbreviation of the trial centre and the consecutive number of the included patient. As all included patients have a bilateral hernia, the randomisation only has to determine which side is operated on and how. The patient is therefore represented in both study groups, with one hernia in each study arm. Randomisation is therefore only between the following two options: "Right side biological and left side synthetic mesh" and "Left side biological and right side synthetic mesh".

Before the start of the study, the biometrician creates a randomisation list for each centre, which assigns the mesh material to the respective treatment side (right/left). Randomisation is stratified by centre and performed as block randomisation (block size 6-10). The randomisation results are announced centrally by telephone by the secretariat of the LKP in Cologne-Merheim ([name]) during regular working hours (elective procedure) in order to monitor the

progress of the study permanently and to be able to unblind the patient in the event of a recurrence (see below). The person entrusted with this task is not involved in the further steps of the study (e.g. follow-up).

As the surgical technique is identical for both sides, it is not possible to be unblinded from the outside by different scars or dressings postoperatively. Both the patient and the hospital staff (except the surgeon) are therefore blinded.

The surgeon cannot necessarily be blinded. Therefore, the follow-up should not be carried out by the surgeon (possibly by someone else from the surgical team).

In the event of a hernia recurrence that necessitates a reoperation, the affected side is unblinded by telephone by the LKP secretariat to enable adequate preparation for the operation. This automatically unblinds the unaffected side as well. When a hernia occurs, the study endpoint is reached for this hernia, but not for the patient. As long as the other side has not yet developed a recurrence, the patient remains in the study with the other hernia. Only when the other hernia also develops a recurrence is this patient's participation in the study terminated.

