#### 4.7.1.2. Further outcomes

In addition to pain and recurrence rates, complications and patient satisfaction are also recorded. For this purpose, the type and number of complications (see also 4.9.1 and 2.3) are analysed, separately for each side where appropriate. The evaluation is performed using the McNemar test for the event rate in paired data.

For patient satisfaction, a side-by-side, descriptive evaluation of the assessment of the overall result, the foreign body sensation and the occurrence of paraesthesia is carried out.

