|-------------------------------|------------------|------------------|---|------------------|------------------|
| Surgery                       |                  |                  | X |                  |                  |
| Imaging (Sonography, MRI, CT) | (X)  | (X)  |   | (X)  | (X)  |
| Complications                 |                  |                  | X | X                | X                |
| Recurrence                    |                  |                  |   | X                | X                |
| Wound infections              |                  |                  |   | X                | X                |
| Haematoma/Seroma              |                  |                  |   | X                | X                |
| Patient satisfaction          |                  |                  |   |                  | X                |

In case of suspected recurrence

These measures are not mandatory for the study and are carried out if requested by the surgeon or anaesthetist. The necessity results from the patient's risk profile.

No time limits are for preoperative preparation and discharge.

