#### 4.9.1.5. CRF: Follow-up 2 years by centres with consultations:

1 week postoperative (+/- 72h), 6 months postoperative (+/- 4 weeks), 1 year postoperative (+/- 2 months), 2 years postoperative (+/- 2 months)

- Date of the follow-up
- Re-hospitalisation (number and duration, date of 1st re-hospitalisation)
- Wound healing of the surgical accesses regular?

- Pain according to VAS (0-10) separated by side
  - At rest
  - Under strain (coughing/pressing)
- Side-separated recurrence
  - In the event of a suspected recurrence, imaging must be performed (sonography/CT or MRI)
- If sonography or other imaging is performed (optional, not mandatory)
  - Seroma/haematoma
- Complications
  - Intestinal injury
  - Bleeding incl. severity (mild/ moderate/ severe)
  - Injury to the bladder
  - Conversion
- Patient satisfaction
- Feeling of foreign body yes/no separated from the side
- Paraesthesia yes/no separated by side

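### Seroma and haematoma are compared between meshes within patients, but the CRF secures their side only when optional sonography is done at discharge, and not at all at follow-up

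*Protocol*

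**What the plan says.** **Outcomes and test.** The Synopsis and Section 2.3 name seroma, haematoma and mesh dislocation among the secondary outcomes. Section 4.7.1.2 has complications analysed by side where this is suitable and adds: "The evaluation is performed using the McNemar test for the event rate in paired data". The Synopsis (Safety) names the same test. Section 6.1.1 reports surgery-specific complications as treated, that is, by the mesh actually placed in each groin. Section 6.1.4 gives secondary outcomes descriptive and exploratory status.

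**Discharge CRF (Section 4.9.1.4).** Under "If sonography is performed (optional, not mandatory" there are two fields, "Seroma/haematoma laterally separated" and "mesh dislocation laterally separated". The complications list that follows has no imaging condition. It repeats mesh dislocation by side and asks for revision operations by side, but its seroma/haematoma entry has no side.

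**Follow-up CRF (Section 4.9.1.5).** Seroma/haematoma appears only under "If sonography or other imaging is performed (optional, not mandatory", with no side. The complications list holds intestinal injury, bleeding, bladder injury and conversion. It contains neither seroma/haematoma nor mesh dislocation.

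**Visit plan (Section 4.7.1.4).** Table 2 marks haematoma/seroma at discharge and at follow-up without condition. The follow-up text collects haematoma/seroma, and mesh dislocation as an example of a complication, again without an imaging condition.

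**Imaging and blinding.** For imaging up to discharge, a footnote to Table 2 says: "These measures are not mandatory for the study and are carried out if requested by the surgeon or anaesthetist", with the need resting on the patient's risk profile. At follow-up the trigger in Table 2 is suspected recurrence. Section 4.6.3 states: "The surgeon cannot necessarily be blinded". It also says that the surgeon should not do the follow-up.

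**The concern.** Each patient carries both meshes, so the side is the treatment. An event without a side cannot be assigned to either mesh. For seroma and haematoma the side is secured only in patients who happen to have sonography before discharge, and from the first week onward the listed CRF content does not secure it at all.

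Two things are at stake. First, the mesh comparison of two named safety outcomes may rest on a small subset imaged at discretion, or may not be possible. Second, if imaging is directed at one groin more often than the other, detection itself may differ between meshes. An analysis plan cannot repair either problem later, because it cannot analyse a side that was never recorded.

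**Working it through.** The protocol gives no seroma, haematoma or imaging rate and no power for these outcomes, so there is no stated figure to reproduce. The check is mainly a comparison of sections.

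**1. What the test needs.** McNemar uses the discordant pairs only: patients with an event on the biological side alone and patients with an event on the synthetic side alone. A yes without a side merges three cells (biological only, synthetic only, both) into one, and the two discordant counts cannot be recovered from it.

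**2. What is collected.**

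| Item | Visit plan (4.7.1.4) | Discharge CRF (4.9.1.4) | Follow-up CRF (4.9.1.5) |
|---|---|---|---|
| Seroma/haematoma | at discharge and follow-up, no condition | side only if sonography is done; unconditional entry has no side | only if imaging is done; no side |
| Mesh dislocation | at follow-up, no condition | by side, also without imaging | not listed |

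For seroma/haematoma, only the sonography block at discharge yields data that step 1 can use. For mesh dislocation, discharge is adequate and follow-up is not. The visit plan and the CRF sections cannot both be followed as they stand.

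**3. Whether unequal imaging could mislead.** This part is illustrative. From the protocol: 451 pairs (Section 6.1.5). Assumed: equal true risk q on both sides, sides independent, probability s that a groin is scanned, share c of events found clinically without a scan, and undetected events counted as absent. Then:

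observed risk on a side = q × [s + (1 − s) × c]

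- q = 10%, c = 0, s = 40% against 20%: 4.0% against 2.0%, or 451 × 0.040 = 18.0 against 451 × 0.020 = 9.0 expected events.
- q = 10%, c = 60%, same s: 0.10 × (0.40 + 0.60 × 0.60) = 7.6% against 0.10 × (0.20 + 0.80 × 0.60) = 6.8%, or 34.3 against 30.7 events.

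Share of trials with p < 0.05 although the meshes are equal (exact two-sided McNemar, 4,000 simulated trials per cell):

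| q | c | both groins together, 30% | 30% vs 20% | 40% vs 20% |
|---|---|---|---|---|
| 5% | 0 | 2.3% | 5.0% | 16.3% |
| 5% | 30% | 3.4% | 3.9% | 6.4% |
| 5% | 60% | 3.0% | 3.2% | 4.0% |
| 10% | 0 | 2.6% | 11.2% | 34.5% |
| 10% | 30% | 3.3% | 5.4% | 13.3% |
| 10% | 60% | 3.5% | 3.8% | 5.2% |
| 15% | 0 | 3.2% | 16.6% | 53.1% |
| 15% | 30% | 3.9% | 7.5% | 18.4% |
| 15% | 60% | 3.5% | 4.7% | 7.5% |

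A separate run with 446 pairs and 20,000 trials (q = 10%, c = 0) gave 10.6% and 33.4% for the two unequal settings, in agreement.

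When both groins are scanned together there is no false signal, but events are lost: at q = 10% and c = 0, the observed rate is 3% instead of 10%.

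**The case against.** A reader might infer more than the protocol supports. The case against the stronger readings is good on these points:

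- **That the result would reflect which patients were scanned.** It would not. Selecting patients affects both sides of a pair alike, as the column for joint scanning shows. Bias needs one groin to be imaged more often than the other. The triggers stated up to discharge are at patient level. The protocol allows unequal imaging but does not describe it.
- **That an unblinded surgeon drives detection.** The request may equally come from the anaesthetist, and after discharge the surgeon should not be the examiner. Patient and other hospital staff are blinded.
- **That mesh dislocation depends on sonography.** At discharge it is recorded by side without imaging. Only its absence from the follow-up list remains.
- **That unscanned sides count as event-free.** The protocol does not say so. A coding rule may sit in the analysis plan, which is not shown, so its absence is not a finding.
- **That a false-positive rate of a third is to be expected.** It requires one groin to be scanned twice as often as the other and nothing to be found clinically. With 60% found clinically the unequal settings give 3.2% to 7.5%.

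It can also be said that Sections 4.9.1.4 and 4.9.1.5 only outline the CRF, that the printed form may ask for the side, and that Section 4.9 takes most CRF data from the patient file, where the side could be looked up. That is possible. But the outline marks the side on neighbouring items and leaves it off here, and recovering it from routine notes is nowhere planned. The contradiction with Table 2 and the follow-up text stands either way.

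**Conclusion.** The point holds as a data collection fault. For seroma and haematoma, the CRF content as written gives a side only for patients with optional sonography at discharge and gives none at follow-up, although the planned paired comparison needs one. The follow-up CRF also drops mesh dislocation. Both conflict with the unconditional collection in Section 4.7.1.4. This conclusion rests on the text alone and on the CRF following the listed content.

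Bias between meshes is a possibility of unknown size. Simulated error with equal meshes runs from about 3%, which is no inflation, to over 30% (53.1% in the most extreme cell), and is decided wholly by assumed scan, event and clinical detection rates. It should not be cited as an expected effect. The outcomes are secondary and exploratory and neither primary endpoint is touched, so priority is modest.

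**What to change.** Reconcile Sections 4.9.1.4 and 4.9.1.5 with Table 2 and the follow-up text in Section 4.7.1.4:

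- Add an unconditional seroma/haematoma field by side at discharge and at every follow-up.
- Add a mesh-dislocation field by side at every follow-up.
- Have these completed at the clinical examination by someone other than the surgeon.
- Use these fields for the McNemar test.
- Record for each side whether it was imaged, and report findings seen only on imaging separately and descriptively.

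The cost is a few CRF boxes at examinations that take place anyway. No additional imaging is needed; in particular, the second groin need not be scanned for this purpose.

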#### 4.9.1.5. CRF: Follow-up 2 years by centres with consultations:

1 week postoperative (+/- 72h), 6 months postoperative (+/- 4 weeks), 1 year postoperative (+/- 2 months), 2 years postoperative (+/- 2 months)

- Date of the follow-up
- Re-hospitalisation (number and duration, date of 1st re-hospitalisation)
- Wound healing of the surgical accesses regular?

- Pain according to VAS (0-10) separated by side
  - At rest
  - Under strain (coughing/pressing)
- Side-separated recurrence
  - In the event of a suspected recurrence, imaging must be performed (sonography/CT or MRI)
- If sonography or other imaging is performed (optional, not mandatory)
  - Seroma/haematoma
- Complications
  - Intestinal injury
  - Bleeding incl. severity (mild/ moderate/ severe)
  - Injury to the bladder
  - Conversion
- Patient satisfaction
- Feeling of foreign body yes/no separated from the side
- Paraesthesia yes/no separated by side

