| Primary study objective:                              | It should be shown that the use of biological mesh material for
laparoscopic hernia treatment results in significantly less
postoperative pain than the use of synthetic mesh material,
without an increased recurrence rate |

Outcome:

Primary Outcome:

- Pain reduction after 6 months measured with a visual analogue scale (VAS 0-10)
- Recurrence rate after 2 years

Secondary Outcome:

- Frequency and intensity of pain at other time points (one week and one year after surgery)
- Recurrence rate after one year
- Local infection of the surgical site
- Mesh dislocation
- Haematoma
- Seroma
- Patient satisfaction (overall result, foreign body sensation, paraesthesia, one week and one year after surgery)

Evaluation criteria:

Effektiviness:

- The expected advantage of the biological mesh is 0.5 points on the 0-10 VAS.
- An assumed recurrence rate after 2 years of 5 % for the synthetic mesh material contrasts with a recurrence rate of  $\leq 8$  % for the biological mesh material.

Security:

- Number and type of complications such as re-interventions or replacement of the mesh

Diagnosis and main  
inclusion criteria:

Diagnosis/main inclusion criterion:

- Patients with bilateral primary inguinal hernias

Further inclusion criteria:

- Patient is suitable for laparoscopic surgery

Main exclusion criteria:

- Recurrent Hernia
- Incarcerated Hernia
- Presence of an acute systemic infection

Test product:

Type of application:

Not two specific products but two types of materials are compared. Each study centre must use commercially available mesh material. However, the following requirements apply:

- CE-certified meshes
- The synthetic mesh materials should be made of polypropylene, polyester or PVDF, have large pores and be lightweight ( $< 100 \text{ g/m}^2$ ).
- The biological mesh material should consist of a perforated, non-crosslinked, acellular and collagenous matrix.
- The meshes should have a minimum size of 10x15 cm
- The meshes can be fixed with adhesive

Comparative therapy,  
dosage and method of  
application:

Both mesh materials are used for each patient and compared directly with each other (self-controlled design). Other procedures/materials are not usual for this indication. The usual laparoscopic implantation in hernia repair is performed according to IEHS guidelines.

Duration of therapy:

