**Safety:**

Complications are compared with the McNemar test for the event rate in paired data.

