## **2.3. Secondary outcome**

- Intensity of pain at other time points (see table Flow Chart)
- Recurrence rates within one year after surgery
- Complications e.g. infections, mesh dislocations
- Haematoma
- Seroma
- Patient satisfaction (overall result, foreign body sensation, paraesthesia) at various points in time (see table flow chart)

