### **Follow-up (1 week +/- 72h, 6 months +/- 4 weeks, 12 months +/- 2 months, 24 months +/- 2 months, 5 und 10 years +/- 2 months postoperative)**

A clinical examination is performed and pain is assessed separately on each side using the VAS (visual analogue scale 0-10). In addition, the presence of a recurrence is evaluated. In the event of a suspected clinical recurrence, confirmation should be made by means of sonography, MRI or CT, which also corresponds to clinical routine.

The incidence of pain after 6 months and the occurrence of a recurrence within the first two years are the two primary endpoints.

Patients can optionally consent to further follow-up visits five and ten years after the operation. The examinations correspond to those of the earlier follow-up visits. If the patients no longer live at the location of the trial centre after ten years, they can be contacted by telephone and asked about the occurrence of recurrences.

The following are also collected

- Complications (e.g. revision surgery, mesh dislocation, haemorrhage)
- Wound infections
- Haematoma/ Seroma

- Patient satisfaction (overall result, foreign body sensation, paraesthesia)

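### The follow-up CRF list of complications (4.9.1.5) repeats the intraoperative list, conflicts with the stated outcomes and visit schedule, and has no side field for the planned paired comparison

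*Protocol*

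**What the plan says.** The synopsis lists local infection, mesh dislocation, haematoma and seroma as secondary outcomes. Its safety criterion is "Number and type of complications such as re-interventions or replacement of the mesh". Section 2.3 repeats the secondary outcomes, with "Complications e.g. infections, mesh dislocations" as one entry and haematoma and seroma as others.

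On analysis, the synopsis states: "Complications are compared with the McNemar test for the event rate in paired data". Section 4.7.1.2 says of the type and number of complications: "see also 4.9.1 and 2.3) are analysed, separately for each side where appropriate", and continues: "The evaluation is performed using the McNemar test for the event rate in paired data". Sections 6.1.1 and 6.1.4 add that complications are reported and compared as treated.

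On collection, section 3.4 makes the CRF the place where complications are documented. The follow-up text in 4.7.1.4 lists "Complications (e.g. revision surgery, mesh dislocation, haemorrhage"), together with wound infections and haematoma/seroma. The flow chart (Table 2) marks complications, wound infections and haematoma/seroma at follow-up.

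The CRF content for the visits from 1 week to 24 months is in 4.9.1.5. Its complications block has four entries: bowel injury, "Bleeding incl. severity (mild/ moderate/ severe"), bladder injury and conversion. Seroma/haematoma stands under a separate condition: "If sonography or other imaging is performed (optional, not mandatory").

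**The concern.** The four follow-up entries describe what can go wrong during an operation. Conversion in particular has no meaning as a finding at a 6- or 24-month visit. The events that the protocol names as postoperative outcomes are not on the list. A centre that completes the form as described would therefore record items that hardly apply, and would have no field for those that do.

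The self-controlled design makes this more serious than an ordinary omission. In a parallel-group trial, an infection recorded per patient still belongs to one arm. Here each patient has one biological and one synthetic mesh, so a complication informs the comparison only if its side is known. No later analysis plan can recover a side that was not recorded. What is at stake is the per-mesh comparison of complications after discharge. Section 4.7.2 makes this part of the rationale: it wants the biological mesh shown to be not inferior for recurrence and/or procedure-related complications.

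**Working it through.** The protocol gives no event rate, power or sample size for the safety comparison, so there is no figure to reproduce. The check sets the lists side by side and asks what the planned test needs.

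**Step 1: operation form against follow-up form.** The complications block of 4.9.1.3 has bowel injury, bleeding with a severity grade, bladder injury and conversion. The block in 4.9.1.5 has the same four in the same order. The discharge form in 4.9.1.4 has a different list that suits the postoperative period: infection, seroma/haematoma, thromboembolism, ileus, revision operation, mesh dislocation and *other*.

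**Step 2: the outcomes traced through the document.**

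| Event | Named as outcome | Follow-up text and flow chart (4.7.1.4) | Discharge CRF (4.9.1.4) | Follow-up CRF (4.9.1.5) |
|---|---|---|---|---|
| Local infection | Synopsis; 2.3 | Yes, no side | Local/systemic, no side | Absent |
| Mesh dislocation | Synopsis; 2.3 | Yes, no side | By side | Absent |
| Haematoma, seroma | Synopsis; 2.3 | Yes, no side, no imaging condition | By side if sonography is done; no side in the complications block | Only under optional imaging, no side |
| Revision, mesh replacement | Synopsis (safety) | Revision surgery, no side | Revision operation, by side | Absent |
| Other | – | – | Yes | Absent |

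Two further items in 4.9.1.5 come near. Wound healing of the surgical accesses is recorded per patient, without side. Re-hospitalisation is recorded as number, duration and date of the first, without reason or side.

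**Step 3: count.** Take the five complication types infection, mesh dislocation, haematoma, seroma and re-intervention. At follow-up, three have no item at all and two have an item that depends on optional imaging. The number with a side-specific item is 0 of 5, at each of the four visits.

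**Step 4: what the test needs.** For a given complication, let *b* be the number of patients with the event on the biological side only and *c* the number with it on the synthetic side only. McNemar's test compares *b* with *c* and uses nothing else. Suppose *k* patients have a one-sided event and the side is not recorded. Then *b* + *c* = *k* is known, but *b* may be anything from 0 to *k*, so the record is compatible with every result from all events on one mesh to all on the other. The as-treated comparison has the same need, because the hernia is assigned to the material implanted on that side.

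**Step 5: is side left out on principle?** No. Section 4.9.1.5 asks for side on pain, recurrence, foreign body sensation and paraesthesia, and 4.9.1.4 does so for revision and mesh dislocation. The gap in the follow-up complications block looks like a list carried over from the operation form.

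**The case against.** The strongest reply is that a list in one section is not the whole of data capture. Section 4.7.1.4 and the flow chart call for these events at follow-up. Section 4.7.1.3 requires notice of any complication to study management within 7 days after discharge and after follow-up visits. Section 4.9 says that CRF data other than patient satisfaction come from the patient file, so the source is not limited to four entries. Section 4.7.1.2 intends analysis by side where that makes sense. The form itself is not shown and may be better than its description.

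This stands in part. A reader might infer that the McNemar comparison after discharge is impossible. The documents do not support that: they contradict each other on what is collected, and side might still be noted on the form, in the notices or in the file. A reader might also infer that the principal coordinating investigator and the safety committee would lack data per mesh. That is speculation: nothing says that the notices omit side, and the allocation is held at the coordinating investigator's secretariat.

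What does not stand is that the other routes close the gap. None of them states a side for complications, and retrieval from patient files is not planned collection. The phrase on analysis by side where appropriate can excuse systemic events such as thromboembolism, but not groin-specific ones such as local infection, seroma or mesh dislocation.

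On weight, both primary endpoints are recorded by side in 4.9.1.5, and under 6.1.4 the secondary outcomes are descriptive and exploratory. That limits the consequence.

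**Conclusion.** The point holds as an inconsistency with a practical consequence. The complications list in 4.9.1.5 is the intraoperative list. It conflicts with the outcomes in the synopsis and 2.3 and with the collection stated in 4.7.1.4 and Table 2. As listed, the follow-up CRF does not supply the paired, side-specific data that 4.7.1.2, 6.1.1 and 6.1.4 rely on for complications after discharge. A smaller gap of the same kind exists at discharge: infection has no side, and seroma/haematoma has one only when sonography is done.

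The size is a count, not a number of lost events: none of the five complication types has a side-specific follow-up item. The conclusion assumes that the form follows 4.9.1.5 as written. This is reasonable, because 3.4 makes the CRF the place of record and 4.7.1.2 points to 4.9.1 for the items analysed, but it cannot be confirmed without the form. It is a matter that should be corrected; it does not threaten the primary analyses.

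**What to change.** Reconcile 4.9.1.5 with 4.7.1.4, the flow chart and 4.9.1.4. Replace the four-item complications list at follow-up with right/left items for:

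- local infection
- seroma
- haematoma (seroma and haematoma whether found clinically or by imaging)
- mesh dislocation
- revision, mesh removal or mesh replacement
- other

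In the complications block of 4.9.1.4, add side to local infection and to seroma/haematoma; systemic infection stays a per-patient item. State in 4.7.1.4 and Table 2 that groin-specific complications are recorded by side, as is already done for pain.

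The cost is a small CRF and database revision and a few more tick boxes per visit. No visit, examination or sample size changes.
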